#### Secondary outcome measures

Secondary outcomes include: (1) systemic inflammatory markers (IL-6, TNF-α); (2) neurological deficit severity assessed by the National Institutes of Health Stroke Scale (NIHSS); and (3) activities of daily living measured by the modified Barthel Index (MBI). All secondary outcomes will be assessed at T0, T1, and T2. The MBI serves both as an operational basis for rehabilitation intensity adjustment and as a secondary outcome measure. To avoid a feedback loop, the adjusted MBI (accounting for rehabilitation dose) will be used as the primary interpretative measure for this secondary outcome, while the raw MBI will be used only for rehabilitation adjustment and will not serve as a direct basis for outcome interpretation. The NIHSS may have a floor effect in the enrolled population; its score changes will be used only as a safety or exploratory reference and will not serve as a primary efficacy measure.

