### Allocation and blinding

This study employs a partial blinding design: participants, responsible clinicians, outcome assessors, and statistical analysts will remain blinded to group allocation, while the intervention providers cannot be blinded due to the visibility of the stimulation site (auricular concha). The intervention providers, rehabilitation therapists, responsible clinicians, and outcome assessors are independent personnel with separate roles; rehabilitation therapists are responsible for conventional rehabilitation training and are not involved in study assessments. An independent research coordinator, who is fully aware of the group allocation, will be responsible for random assignment and allocation concealment. In the event of a serious adverse event, the responsible clinician will decide whether to unblind, and will record the time, reason, and signature of unblinding. The unblinding information will be disclosed only to the extent necessary for treatment. The rehabilitation therapists will remain blinded to group allocation; they will adjust rehabilitation intensity solely based on Brunnstrom stage and modified Barthel Index scores, and will not be involved in the administration of taVNS or sham stimulation, nor have access to group allocation information.

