Both groups will receive standardized conventional rehabilitation training delivered by the same rehabilitation team during the intervention period (weeks 1–4), consisting of 4 weeks, 5 days per week. The training includes: physical therapy (once daily, 40 min): positioning and transfer training (5 min), affected lower limb weight-bearing training (10 min), sit-to-stand transfer training (10 min), balance training (10 min), and walking training (5 min); and occupational therapy (once daily, 30 min): activities of daily living training (e.g., dressing, eating, grooming) and upper limb functional training. All training will be supervised one-on-one by uniformly trained therapists. Training intensity will be assessed every 5 days according to the patient's Brunnstrom stage and modified Barthel Index score, following an individualized progression principle. Training performance will be recorded in a standardized training log and reviewed weekly by the study coordinator. Adjustments to the duration of individual modules based on the patient's functional characteristics are permitted, provided the total duration remains unchanged; however, adding or removing training modules is not allowed. During the follow-up period (weeks 5–8), participants will continue to receive the same conventional rehabilitation training as in the intervention period (with unchanged content, frequency, and supervision), but will no longer receive taVNS or sham stimulation. Training performance will continue to be recorded and reviewed.

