### Data collection

Demographic characteristics (age, sex, education level), stroke-related medical history (disease duration, stroke type, lesion location), comorbidities, and current medication lists will be collected for all participants and recorded in the case report form. During the 2-week period before baseline and throughout the trial, medications affecting heart rate, heart rate variability, exercise tolerance, or inflammation (including beta-blockers, calcium-channel blockers, antiarrhythmic agents, anticholinergic medications, antidepressants, sedatives, corticosteroids, and other anti-inflammatory agents) will be maintained at stable doses unless medically indicated otherwise. Any medication adjustments will be documented in detail (drug name, dose, reason for adjustment, and date), and will be included as covariates in the final statistical analysis. The actual duration, intensity, completion rate, and content of rehabilitation training will be recorded separately for each group. Physical activity outside the study and additional rehabilitation interventions will be documented through weekly follow-up interviews. In the final report, the number and reasons for all screening failures will be recorded, particularly the proportion of patients excluded due to inability to complete CPET.

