### Statistical methods

Statistical analyses will be performed using SPSS 26.0 and R 4.1.0, following the intention-to-treat principle. All tests will be two-sided, with a significance level of *α* = 0.05 unless otherwise specified for multiple comparisons. Statisticians will remain blinded to group allocation until data lock. All randomized participants will be retained in the intention-to-treat analysis. The per-protocol analysis will report the proportion and characteristics of participants who do not meet the effort criteria. Additional stratified analyses will be considered: (1) all randomized participants; (2) those meeting adequate-effort criteria; (3) those terminating due to cardiopulmonary limitation; and (4) those terminating due to neurological or motor limitation, to assess the robustness of the results. For the primary outcome, VO_2_peak will be analyzed using a linear mixed-effects model, with group, time, and their interaction as fixed effects and participant as a random effect (random intercept) to account for within-subject correlations; a random slope may be added if model fitting requires. Age, sex, baseline VO_2_peak, stroke type, disease duration, baseline National Institutes of Health Stroke Scale score, and recruitment source (hospital or community) will be included as prespecified covariates. In the model, the time factor (T0, T1, T2) is used to estimate longitudinal trends, while baseline VO_2_peak is included solely as a covariate to adjust for baseline differences; the two serve different functions and do not constitute redundant adjustment. The covariance structure will be selected from unstructured, compound symmetry, or first-order autoregressive models based on the Akaike information criterion or Bayesian information criterion. The primary treatment effect will be assessed based on the baseline-adjusted between-group difference in VO_2_peak at T1, and the effect estimate, 95% confidence interval, and corresponding *p*-value will be reported. For secondary outcomes, all four measures (interleukin-6, tumor necrosis factor-alpha, National Institutes of Health Stroke Scale, and modified Barthel Index) will be analyzed longitudinally using the same linear mixed-effects model as for the primary outcome. For variables with substantial deviation from normal distribution or violations of parametric assumptions, generalized linear mixed models or nonparametric methods will be used as supplements. To control for multiple comparisons, a Bonferroni correction will be applied for the four secondary outcomes, with the significance threshold set at *α* = 0.05/4 = 0.0125. The exploratory outcome (heart rate variability) will not be adjusted for multiple comparisons and will be used only for exploratory interpretation. For missing data, the primary analysis will use the linear mixed-effects model under the missing-at-random assumption, utilizing all available observed values. To assess robustness, multiple imputation by chained equations and per-protocol analysis will be conducted as sensitivity analyses. In addition, the originally prespecified repeated-measures analysis of variance will be performed as a complementary analysis for comparison with the primary results; if the sphericity assumption is violated, the Greenhouse-Geisser correction will be applied, and *post-hoc* comparisons will be performed using the Bonferroni method. The incidence of adverse events will be compared using Fisher's exact test. If the sample size permits, prespecified exploratory subgroup analyses will be conducted for stroke type (ischemic vs. hemorrhagic) and recruitment source (hospital vs. community), using interaction tests to assess potential effect modification, with results interpreted only as exploratory. Due to sample size constraints (80 participants per group), stratification was performed only for age and disease duration. Other heterogeneity factors, including stroke type, baseline NIHSS score, and baseline VO_2_peak, have been incorporated as prespecified covariates into the linear mixed-effects model for adjustment.

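### The MBI is to be interpreted after adjustment for rehabilitation dose, and on-trial medication changes are to be covariates; both arise after randomisation, can distort the treatment effect, and conflict with the stated analysis model

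*Protocol article*

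**What the plan says.** **MBI.** Under Secondary outcome measures, the protocol notes that the MBI both guides rehabilitation intensity and is an outcome. Its answer to this circularity is that "the adjusted MBI (accounting for rehabilitation dose) will be used as the primary interpretative measure for this secondary outcome". The unadjusted score is given a different role: "the raw MBI will be used only for rehabilitation adjustment and will not serve as a direct basis for outcome interpretation".

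**How dose is set.** Under Intervention: "Training intensity will be assessed every 5 days according to the patient's Brunnstrom stage and modified Barthel Index score". Under Allocation and blinding, the blinded therapists have no other input: "they will adjust rehabilitation intensity solely based on Brunnstrom stage and modified Barthel Index scores". Module times may vary, "provided the total duration remains unchanged", and modules may not be added or removed. Data collection records actual duration, intensity, completion rate and content.

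**Medication.** Data collection asks for stable doses of drugs affecting heart rate, HRV, exercise tolerance or inflammation, from 2 weeks before baseline and throughout the trial, unless a change is medically indicated. It then says: "Any medication adjustments will be documented in detail (drug name, dose, reason for adjustment, and date), and will be included as covariates". The sentence ends by naming the final analysis as the place where they enter.

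**Model.** Statistical methods lists seven prespecified covariates: age, sex, baseline VO2peak, stroke type, disease duration, baseline NIHSS and recruitment source. The four secondary outcomes, MBI among them, "will be analyzed longitudinally using the same linear mixed-effects model as for the primary outcome", each tested at 0.05/4 = 0.0125. The primary effect is the baseline-adjusted group difference in VO2peak at T1. Neither rehabilitation dose nor medication change appears in that section.

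**The concern.** Rehabilitation dose is not a baseline characteristic. It follows the MBI and Brunnstrom stage after randomisation, and the Discussion itself suggests that taVNS may promote motor recovery. If active stimulation raises these scores, it changes the dose. A model that holds dose constant then no longer estimates the whole effect of being assigned to taVNS. Because blinded therapists act only on the two scores, an arm difference in prescribed intensity can come only from chance or from a treatment effect on those scores. There is no therapist bias for the adjustment to remove, and adjusting does not undo the feedback loop.

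Medication changes made during the trial raise the same problem if they enter the efficacy models. The drugs named act on heart rate, autonomic balance or inflammation, the pathways through which taVNS is hypothesised to work.

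Two sets of rules for the same outcome also leave a choice of model that could be made after the results are seen.

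**Working it through.** **1. The passages side by side**

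| Item | Secondary outcome measures / Data collection | Statistical methods |
|---|---|---|
| Main MBI analysis | Adjusted for rehabilitation dose; raw MBI not used for interpretation | Same model as VO2peak; no dose term |
| Medication changes | Covariates in the final analysis | Not among the seven covariates |

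Both columns cannot be followed. This needs no arithmetic. The one stated figure tied to the MBI test reproduces: 0.05/4 = 0.0125.

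**2. Adjusting MBI for dose**

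The documents give no input for the size of the bias, so everything here is assumed. Let T be arm, D dose and Y final MBI, with D and Y in SD units, and let U be unmeasured prognosis:

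- D = a·T + c_D·U + noise
- Y = (total − a·b)·T + b·D + c_Y·U + noise

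Here a is the shift in dose caused by treatment, b the effect of dose on MBI, and c_D and c_Y the loadings of prognosis. Regressing Y on T alone returns the total effect. Regressing Y on T and D returns

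adjusted effect = total − a·(b + c_D·c_Y).

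With b = 0.3 and c_D = c_Y = 0.4, the bracket is 0.3 + 0.16 = 0.46. For a true total effect of 0.50 SD:

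| a (SD) | Adjusted effect | Loss | Simulated effect | Simulated power at 0.0125 |
|---|---|---|---|---|
| 0 | 0.50 | 0% | 0.495 | 72% |
| 0.2 | 0.50 − 0.092 = 0.408 | 18% | 0.408 | 52% |
| 0.3 | 0.50 − 0.138 = 0.362 | 28% | 0.361 | 40% |
| 0.5 | 0.50 − 0.230 = 0.270 | 46% | 0.266 | 17% |

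Simulation used 64 per arm and 4,000 runs. Without D in the model, the estimate stayed at about 0.50 SD with power of 61–62%. With a true total effect of zero, the adjusted estimate was −0.14 SD (a = 0.3) and −0.23 SD (a = 0.5), with false rejection of 5.1% and 13.5% against 1.25%. With a = 0 there was no bias.

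A second model sets intensity to 0.8 × interim MBI plus noise of SD 0.3, 0.6 or 1.0. The effect falls from 0.395, 0.392 and 0.394 SD to 0.285, 0.324 and 0.349 SD, a loss of 28%, 17% and 11%. Weaker coupling brings the loss close to nil.

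The a = 0.5 row moves dose by as much as the entire assumed effect on MBI. With session time and modules fixed it is an extreme, so the summary range stops at about 28%.

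**3. Adjusting VO2peak for medication changes**

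Assume no true VO2peak effect, change rates p0 (sham) and p1 (active), and a latent tendency to change medication that correlates r in size with lower fitness. With φ the normal density at the cut-off for each rate,

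γ = r × mean(φ0, φ1) / mean[p0(1 − p0), p1(1 − p1)], and spurious effect = γ × (p1 − p0).

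Example, 10% vs 30%, r = 0.5: mean φ = (0.1755 + 0.3477)/2 = 0.2616; mean variance = (0.09 + 0.21)/2 = 0.15; γ = 0.5 × 0.2616/0.15 = 0.872; effect = 0.872 × 0.20 = 0.17 SD.

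| Sham vs active | r = 0.3 | r = 0.5 |
|---|---|---|
| 20% vs 20% | 0 | 0 |
| 5% vs 10% | 0.03 | 0.05 |
| 10% vs 15% | 0.03 | 0.05 |
| 15% vs 30% | 0.08 | 0.13 |
| 10% vs 30% | 0.10 | 0.17 |

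For scale, the planning value f = 0.25 corresponds to d = 2 × 0.25 = 0.50 SD.

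**The case against.** A reader might infer that the trial's estimates are biased as a matter of course. The documents do not support that. The bias vanishes if treatment moves neither dose nor medication, and several rules limit the movement: total training time and frequency are fixed, modules cannot be added or dropped, drug doses are to stay stable, and the responsible clinicians are blinded. Rates of 10–15% versus 30% are an adverse case, and modest imbalances give only 0.03 to 0.05 SD. All of this stands.

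A reader might also infer that the primary VO2peak result is compromised. Data collection refers only to the final statistical analysis and does not name the primary model. Statistical methods defines the primary effect as baseline-adjusted and lists its covariates without medication. Part of the medication sentence covers the 2 weeks before baseline, and changes made then are harmless as covariates. The risk to VO2peak depends on how one ambiguous sentence is read.

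Finally, the protocol does not say how dose will be accounted for, and an analysis plan not shown may do so. An effect net of extra rehabilitation is a legitimate question. But it is a different question from the effect of assignment, simple covariate adjustment would not answer it cleanly, and a later plan would still face a protocol that rules out interpreting the raw MBI. The objection limits the size and reach of the point. It does not remove the contradiction or make dose a baseline variable.

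**Conclusion.** For MBI, the plan is wrong as written. Its main interpretative measure conditions on a variable that the outcome itself drives after randomisation, and this conflicts with the model given in Statistical methods. As a covariate adjustment it can remove or distort part of the treatment effect. The loss runs from almost nil to about 28%, depending on how strongly MBI moves dose, and it is larger only under an extreme shift.

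For medication, the covariate rule and the covariate list disagree. If on-trial changes enter the efficacy models and their rates differ by arm, the estimates can be biased: by about 0.03 to 0.05 SD for modest imbalance and 0.08 to 0.17 SD for 10–15% versus 30%. The rates, correlations and coupling strengths are all assumptions.

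The firm defect concerns one of four secondary outcomes and a covariate rule that has to be reconciled. It should be fixed, but it does not show that the primary analysis is invalid.

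**What to change.** - **Secondary outcome measures:** make the Statistical methods model for MBI (baseline covariates only, no dose term, compared by randomised arm) the main MBI analysis. Remove the statement that bars the raw MBI from interpretation. Report rehabilitation dose by arm.
- **Data collection:** limit medication covariates to use or changes before randomisation, and report later changes by arm.
- **Statistical methods:** label any model adjusted for dose or on-trial medication as exploratory or sensitivity, and bring the three sections into agreement. Adding baseline beta-blocker use to the covariate list is optional.

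The cost is wording in three sections. The data are already to be collected, and no treatment, visit or sample size changes. Recruitment is planned from July 2026, so a change made before then cannot be suspected of following the results.

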### Inflammatory marker assessment

At T0, T1, and T2, between 8:00 and 9:00 a.m. (before cardiopulmonary exercise testing), fasting venous blood samples (5 mL, EDTA anticoagulant tube) will be collected from participants after an overnight fast of at least 8 h. Within 30 min after collection, the samples will be centrifuged at 4 °C and 3,000 rpm for 15 min to separate plasma, which will then be aliquoted and stored at −80 °C. Concentrations of interleukin-6 (IL-6) and tumor necrosis factor-alpha (TNF-α) will be uniformly measured using enzyme-linked immunosorbent assay (ELISA; R&D Systems).

### Mechanistic exploration

To explore potential associations between taVNS-mediated improvement in cardiorespiratory fitness and changes in autonomic function, resting-state electrocardiograms (5 min recordings) will be obtained at T0, T1, and T2. Time-domain (SDNN) and frequency-domain (HF) indices of heart rate variability will be analyzed as exploratory outcomes. These indices will not be subjected to multiplicity correction and will be used solely for exploratory purposes, not for causal inference.

Inflammatory markers (IL-6, TNF-α) remain secondary outcome measures, but their mechanistic interpretation is limited to exploratory analysis. No mediation model is prespecified, and these results will not be used for causal inference.

### Safety assessment

Any adverse events occurring during the intervention period, including but not limited to local skin irritation, erythema, dizziness, palpitations, nausea, headache, and tinnitus, will be recorded and reported by the research coordinator. Investigators will assess the causal relationship between adverse events and the intervention, as well as their severity. Serious adverse events will be immediately reported to the ethics committee, and appropriate medical measures will be taken according to clinical needs.

### Sample size calculation

The sample size for this study was estimated based on the group-by-time interaction effect for the primary outcome, VO_2_peak. Given the current lack of direct prior data on the effect of taVNS on VO_2_peak in stroke patients, we referred to the standardized effect size (*d* = 0.58) reported in a randomized controlled trial in healthy populations (25). Considering the greater heterogeneity in stroke patients, a conservative moderate effect size assumption was adopted for sample size planning. The sample size calculation was based on the group-by-time interaction from repeated-measures ANOVA, while the primary analysis will use a linear mixed-effects model; the two approaches are consistent in their handling of repeated-measures data, and LMM is more robust to missing data, so the sample size adequacy is unaffected. *A priori* power analysis was performed using the *F* tests—ANOVA: Repeated measures, between–within interaction module in G * Power 3.1 software, with the following parameters: effect size *f* = 0.25, *α* = 0.05, power (1 − *β*) = 0.80, number of groups = 2, number of measurements = 3, correlation among repeated measures = 0.50, and non-sphericity correction *ε* = 0.75. The effect size conversion was based on the formula *f* = *d*/2 (for two-group comparisons), with *d* = 0.58 (healthy populations) converted to *f* = 0.25 (stroke patients). A conservative estimate was adopted considering the greater heterogeneity expected in stroke patients. The assumed correlation among repeated measures (*ρ* = 0.50) was based on the typical range (0.3–0.7) reported in similar stroke rehabilitation studies, taking the median value; the non-sphericity correction (*ε* = 0.75) was set as a conservative value recommended by the G * Power software manual. Under these assumptions, the required total sample size was estimated to be approximately 128 participants, i.e., approximately 64 per group. Accounting for a 20% dropout rate, a final sample size of 160 participants (80 per group) was planned. Given the current lack of direct data on the effect of taVNS on VO_2_peak in stroke patients, this study adopted a conservative estimate based on the effect size from healthy populations; future research may further define the clinically meaningful difference in this population.

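### The 128 participants do not follow from the stated repeated-measures inputs, which give 34, and the test that was powered is not the primary T1 comparison

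*Protocol article*

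**What the plan says.** The section Sample size calculation names the repeated-measures between-within interaction module of G*Power 3.1. It gives "effect size *f* = 0.25", alpha 0.05, power 0.80, two groups, and "number of measurements = 3, correlation among repeated measures = 0.50, and non-sphericity correction" 0.75. It then states: "Under these assumptions, the required total sample size was estimated to be approximately 128 participants, i.e., approximately 64 per group". A 20% dropout allowance raises this to 160.

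The effect size starts from d = 0.58 in a trial in healthy people. The protocol cites f = d/2 and reports the step as "with *d* = 0.58 (healthy populations) converted to *f* = 0.25 (stroke patients"), adding that a conservative value was chosen because stroke patients are more heterogeneous.

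The same section acknowledges a change of model: "The sample size calculation was based on the group-by-time interaction from repeated-measures ANOVA, while the primary analysis will use a linear mixed-effects model". It argues that both approaches handle repeated measures consistently, "so the sample size adequacy is unaffected".

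The section Outcome measures makes T1 the primary efficacy time point. Statistical methods fixes the test: "The primary treatment effect will be assessed based on the baseline-adjusted between-group difference in VO_2_peak at T1".

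**The concern.** The paragraph gives every input that the named module needs, so the result can be checked, and it fails the check by a factor of nearly four. The conversion from d to f also fails on its face, and f = d/2 belongs to a two-group comparison at one time point, not to an interaction. Finally, the powered hypothesis (a 2-df interaction over T0, T1 and T2) differs from the primary one (a 1-df contrast at T1). The defence offered compares ANOVA with the mixed model and does not address the change in the effect being tested.

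This paragraph is the published justification for a sample size that was amended from 92 to 160 (Ethics and dissemination). As it stands, a reader cannot say from the stated calculation what difference in VO2peak at T1 the trial is powered to detect.

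**Working it through.** **1. The stated inputs.** From Sample size calculation: f = 0.25, alpha = 0.05, k = 2 groups, m = 3 measurements, rho = 0.50, epsilon = 0.75, target power 0.80. For the between-within interaction:

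- noncentrality: lambda = f² · N · m · epsilon / (1 − rho) = 0.0625 × N × 3 × 0.75 / 0.50 = 0.28125 N
- df1 = (k − 1)(m − 1) epsilon = 1.5
- df2 = (N − k)(m − 1) epsilon = 1.5 (N − 2)

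| Total N | lambda | Power |
|---|---|---|
| 32 | 9.00 | 78.4% |
| 34 | 9.56 | 81.0% |
| 128 | 36.00 | above 99.9% |

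The inputs therefore need N = 34.

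**2. Other readings of the inputs.**

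- Effect size on a scale that does not use rho, lambda = f² · N · (m − 1) · epsilon: N = 98, and about 90% power at 128. Using N − 2 in place of N also gives 98.
- rho over the protocol's quoted range of 0.3 to 0.7, default scale, epsilon 0.75: N = 46 down to 22.
- Between-groups module at rho = 0.50: N = 86.

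None of these gives 128.

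**3. What does give 128.** A two-sample t-test with d = 0.50 and 64 per arm has noncentrality 0.50 × √(64/2) = 2.83 on 126 df, and power 80.1%. With 63 per arm the power is 79.5%. The dropout step is right: 128 / (1 − 0.20) = 160.

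**4. The effect-size conversion.** 0.58 / 2 = 0.29, not 0.25. The value 0.25 corresponds to d = 0.50.

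Next, assume no group difference at T0 and a difference d at T1 and T2. The differences (0, d, d) have mean 2d/3, so the deviations are (−2/3, 1/3, 1/3)d. Half of each deviation falls to each group: (−1/3, 1/6, 1/6)d. The mean square is (4 + 1 + 1)/36/3 · d² = d²/18, so f = d/√18 = 0.236d. The profile (0, d, 0) gives the same f.

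- f = 0.25 entered as an interaction implies d = 0.25 / 0.236 = 1.06 SD.
- d = 0.50 implies f = 0.118. With rho = 0.50 and epsilon = 0.75, N = 128 gives 75.2% and N = 144 is needed. With epsilon = 1, N = 128 gives 83.6% and N = 118 suffices.

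**5. The actual primary contrast.** Group difference at T1, two-sided alpha 0.05, 64 evaluable per arm. Baseline adjustment multiplies the SD by √(1 − rho²), where rho is the baseline-to-T1 correlation. The rho values below are assumptions taken from the protocol's range.

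| rho | SD factor | Power at d = 0.50 | Detectable d at 80% power |
|---|---|---|---|
| unadjusted | 1.000 | 80.1% | 0.50 |
| 0.3 | 0.954 | 83.7% | 0.48 |
| 0.5 | 0.866 | 90.0% | 0.43 |
| 0.7 | 0.714 | 97.6% | 0.36 |

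If all 80 per arm are analysed, the unadjusted power at d = 0.50 is 88%. At 34 in total (17 per arm) it would be 29%, so the answer from the stated inputs is not a usable sample size either.

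**The case against.** The best reply is that nothing in the design has to change. N = 160 gives at least 80% power for the T1 contrast at d = 0.50, repeated-measures ANOVA is retained as a complementary analysis, and a reader who inverts f = d/2 will recover d = 0.50 and recognise the familiar 64 per arm. That is right about the design. It does not rescue the derivation: the stated module and inputs do not produce the stated number, and the adequacy of N for the T1 contrast is never argued.

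Three narrower objections have force.

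- **Origin of 128.** The t-test match does not prove how 128 was obtained. The stated module with f = 0.125 also returns 128, as does a scale that ignores rho with epsilon = 0.50. The authors should say what was run.
- **The 75% figure.** Power for d = 0.50 read as an interaction depends on the assumed effect profile and on epsilon. It is 75.2% at the protocol's epsilon and 83.6% at epsilon = 1, the value that equal correlations with equal variances imply. It should not be read as a demonstrated shortfall.
- **0.29 against 0.25.** The protocol does disclose a conservative reduction. The fault is in calling it a conversion and in giving no reason for its size.

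**Conclusion.** The concern holds. The listed inputs require 34 participants, or 98 on the effect-size scales that ignore the stated correlation; none of the readings that keep the listed inputs gives 128. The conversion is wrong as arithmetic and belongs to a different kind of comparison. The powered test is not the primary test, so the reasoning behind the adequacy statement fails, although 128 evaluable participants do suffice for the T1 contrast at d = 0.50.

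The error lies in the justification and not in the number to be recruited. It must still be corrected, because the published power claim is false as written and anyone who reruns the module will see it. The result of 34 rests on the default effect-size option, the one that uses the stated rho. The adjusted power figures rest on an assumed baseline-to-T1 correlation of 0.3 to 0.7 and on 64 evaluable participants per arm.

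**What to change.** Keep 160 participants and replace the calculation with one for the primary contrast:

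- Test: baseline-adjusted difference in VO2peak (mL/kg/min) at T1, two-sided alpha 0.05, 64 evaluable per arm after 20% loss from 80.
- Effect: d = 0.50, described as a judgement-based discount from 0.58, with the reason for its size.
- Power: 80% without and about 90% with baseline adjustment at an assumed correlation of 0.50. Give the range over 0.3 to 0.7 (84% to 98%; detectable d 0.48 to 0.36).
- Clinical units: state an SD for VO2peak with its source, and give d × SD in mL/kg/min. The protocol contains no SD, so this needs a new input.

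Delete the repeated-measures ANOVA inputs, the f = d/2 step and the sentence that the change of model leaves adequacy unaffected. State what was actually run to obtain 128.

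The cost is one rewritten paragraph, plus the registry text if it repeats the calculation. The sample size and the analysis do not change. Recruitment is planned from July 2026, so the correction should be made before enrolment starts.
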